## Abstract

**Background:**

Suicidal behaviour and deliberate self harm are common among adolescents. Limited evidence exists regarding interventions that can reduce risk; however research indicates that maintaining contact either via letter or postcard with at-risk adults following discharge from services can reduce risk. The aim of the study is to test a postcard intervention among people aged 15-24 who presented to mental health services but are not accepted, yet are at risk of suicide.

**Methods/design:**

The study is a 3-year randomised controlled trial conducted at Orygen Youth Health Research Centre in Melbourne Australia. Participants are young help-seekers aged 15-24 who are at risk of suicide. Participants will be recruited over a 12 month period. The intervention comprises a regular postcard to be sent monthly for 12 months. The postcard enquires after their well being and includes information regarding individual sources of help and evidence-based self help strategies. Participants are assessed at baseline, 12 and 18 months.

**Discussion:**

This paper describes the development of a study which aims to reduce suicide risk in a sample of young help-seekers. If effective, this intervention could have significant clinical and research implications for a population who can be hard to treat and difficult to research.

**Trial Registration:**

The study was registered with the Australian Clinical Trials Registry; number: ACTRN012606000274572.

## Background

Suicidal and self-harming behaviour, including suicidal ideation, are common amongst adolescents. Among secondary school students, approximately 5-7% report having engaged in deliberate self-harm (DSH) in a 12 month period, whilst lifetime rates are 12-13% [1,2]. As many as 60% reported suicidal ideation [3].

Suicidal behaviour, is associated with a range of negative outcomes, most notably risk of further suicidal behaviour and completed suicide [4,5] and other forms of premature mortality such as accidental death and homicide [6]. A key risk factor for suicidal behaviour is mental disorder [7], particularly affective disorders and/or depressive symptoms [7,2]. However, mental disorders are not present in all young people at risk and suicidal behaviour is often precipitated by adverse life events or interpersonal crises [7].

Whilst much is known about the epidemiology of suicidal behaviour, less evidence exists regarding interventions to reduce risk [8], particularly that from randomised-controlled trials [9]. One promising intervention, tested in adults, has a focus on maintaining contact with those at risk. Two studies have shown that contact via regular letter or postcard with at-risk adults, after discharge from an inpatient psychiatric unit [10] or an Emergency Department (ED) [11] reduced subsequent suicidal behaviour for up to two years [10]. The treatment effect may be due to enhancing connectedness and perceived social support [12,11]. Treatment approaches that are successful among adults may not be among young people [13] and it is unknown whether the 'postcard' intervention would be successful with adolescents and young adults.

Research at a specialist mental health service (ORYGEN Research Centre, ORC) had showed that while a number of young people were not unwell enough to meet the entry criteria, this group included many individuals who had made suicide attempts (n = 14; 25%) or expressed suicidal ideation (n = 22; 38.6%) [14]. This highlighted a service provision gap that could potentially be filled by a postcard intervention.

## Methods/design

### Aims and hypotheses

The aims are to determine if suicidal and self harming behaviour can be reduced by the receipt of a regular postcard sent monthly over 1 year.

The hypotheses are that the receipt of a regular postcard will result in: 1. Decreased suicidal behaviour and ideation 2. A reduction in depression and hopelessness 3. Improved self-esteem 4. Increased perceived social support, and 5. Increased help seeking. We further hypothesise that: 6. There will be a positive association between reductions in suicidal behaviour and improved self-esteem and perceived support, and 7. Between reduced suicidal behaviour and hopelessness and depression.

### Study design

The study is a randomised controlled trial registered with the Australian Clinical Trials Registry and approved by the North Western Mental Health Research and Ethics Committee.

### Setting

Orygen Youth Health (OYH) is a publicly funded specialist mental health service for people aged 15-24 living in the Western and Northwestern regions of Melbourne. The service treats individuals with both psychotic and non-psychotic disorders. There is also a triage service, where eligibility for treatment is determined. It also houses Orygen Youth Health Research Centre (OYHRC).

### Participants

Participants will be recruited from OYH triage over a 12 month period. Inclusion criteria are: 15 to 24 years; resident in Northwestern Metropolitan region of Melbourne; refused from service; current or lifetime history of suicidal ideation or attempts or DSH. These will be assessed by a Research Assistant (SG) via the written triage records. Exclusion criteria are: known organic cause for presentation; intellectual disability; inability to speak English. The participant flow chart is shown in Figure 1.

**Figure 1 F1:**
[figure not shown]
**Study flow-chart: This figure displays the participant flow-chart**.

### Procedure

After assessing eligibility, the Research Assistant will telephone the young person to explain the study and seek informed consent. If the young person is interested in participating, the Research Assistant will arrange a face-to-face interview, during which written information will be provided and consent sought. Once consent is obtained the Research Assistant will conduct the baseline interview.

Following the baseline interview the study coordinator (JR) will contact each participant by telephone (within 1 to 5 days), enquire about wellbeing and ask him or her to identify 3 sources of help that may be useful in times of crisis. It will be explained that this information would be included in a postcard should the young person be allocated to the intervention group.

### Intervention

The intervention is a regular postcard sent in a sealed envelope. One postcard a month is sent over 12 months, starting the month after the baseline assessment. The postcards have been designed with a 'youth focus', in conjunction with the OYHRC consumer group. They all enquire about the person's well being, remind them about the sources of help identified during the telephone interview and promote one of 6 evidence-based self-help strategies. These are: 1. Physical activity 2. Early morning light exposure 3. Self-help books based on cognitive behavioural therapy 4. Websites known to be effective e.g. BluePages [15] and Mood GYM [16] 5. Relaxation training 6. Reducing alcohol and other substance use [15-18]. The self-help strategies and the individual sources of help will be rotated. The participant's name and the individual source of help obtained from telephone interview will be hand-written and each postcard individually signed. An example of the postcard is shown in Figure 2.

**Figure 2 F2:**
[figure not shown]
**Postcard: This figure contains an example of the postcard used in the study**.

Included with each postcard will be a 'change of address' slip, as well as the option for participants to request that the postcards be discontinued.

### Control intervention

Those in the control group will receive the initial 'sources of help' interview but no postcards.

### Outcomes

The primary outcomes are suicidal behaviour and ideation, DSH, hopelessness, depression, self-esteem, help-seeking and perceived social support, with assessment at baseline, 12 and 18-months. The acceptability of the intervention will also be assessed by calculating the proportion of participants who choose to discontinue receiving the postcards and via an evaluation questionnaire administered at 12-month follow-up. This questionnaire also asks participants whether or not they had employed any of the help-seeking strategies recommended in the postcards.

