### Sample size calculation: effect size and statistical power

Suicide and SA rates from other studies vary between 3.9% and 15.1% for a contact group, and 4.6% and 17.3% for a non-contact group [11,10], with small effect sizes. The design of our study differs from previous studies and it is not possible to make any firm inference for our study, although it is reasonable to expect a similar effect size. The power analysis for this study is based on using the general linear model to compare the intervention and control groups with the baseline values of an outcome measure as the covariate. It is assumed (conservatively) that the covariate would explain 5% of the variance in the dependent variable. Based on previous research at this centre, we expect to recruit 180 subjects who would be equally allocated to the two groups and conservatively estimated a drop-out rate of 20%. A power calculation indicated that we would be able to detect a small effect size of 0.21 with a significance level of 0.05 and power of 0.8. The actual sample size (n = 165) has made only a small change to the power calculation - the detectable effect size has increased from 0.21 to 0.22.

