### Statistical methods

At each follow-up time point the general linear model will be used to test for the treatment factor, i.e. to compare the intervention and control groups for each outcome measure. The corresponding baseline values of each outcome measure will be used as the covariate. In addition, the effects of other possible predictors (such as gender and age) on outcome will be explored. Multi-level modeling will be used to compare the trend over time for each outcome in the two groups. Both the last observation carried forward and multiple imputation techniques will be considered if the amount of missing values is substantial.

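### Seven or eight outcomes are all called primary at two follow-ups, with no lead outcome or time point and only an undivided 0.05 level in view

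*Protocol article*

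**What the plan says.** The Outcomes section of the protocol article states: "The primary outcomes are suicidal behaviour and ideation, DSH, hopelessness, depression, self-esteem, help-seeking and perceived social support". Timing is given for the whole list at once, "with assessment at baseline, 12 and 18-months", so no follow-up has priority.

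Statistical methods says "At each follow-up time point the general linear model will be used to test for the treatment factor", and that the model serves "to compare the intervention and control groups for each outcome measure". It then adds: "Multi-level modeling will be used to compare the trend over time for each outcome in the two groups". It gives no significance level.

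The one level in the document is in the sample size section, where the trial is said to be able to "detect a small effect size of 0.21 with a significance level of 0.05 and power of 0.8". That calculation concerns a generic outcome measure with its baseline value as covariate. It names no scale and no follow-up.

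Aims and hypotheses does point to a domain. The aim concerns suicidal and self-harming behaviour, and hypothesis 1 concerns suicidal behaviour and ideation. Hypotheses 2 to 5 cover the other constructs. The numbering is not described as an order of testing, and Outcomes does not carry the aim's emphasis through.

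**The concern.** A primary outcome fixes in advance which result decides whether the intervention worked. Here that label is spread over seven or eight constructs and two follow-ups. A nominally significant difference in self-esteem at 18 months, with no change in suicidal behaviour, would count as a primary result on the same footing as a fall in self-harm at 12 months.

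This matters because the Discussion looks ahead to wide use if the postcards prove effective, including as a control treatment in later trials of people at risk. With many equal primaries, an effectiveness claim could rest on whichever comparison happened to come out, and 0.05 would not describe the error rate of that claim.

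**Working it through.** **The plan's own figure.** The document states no familywise error rate. Its only related figure is the detectable effect size: 0.21 for 180 recruited and 0.22 for the actual 165.

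- A two-group analysis of covariance (noncentral F, two-sided 0.05, power 0.80) returns these values as Cohen's f with all 180 and 165 analysed and no gain from the covariate: 0.210 and 0.219.
- With all the stated inputs, that is 20% drop-out (180 × 0.8 = 144; 165 × 0.8 = 132) and 5% of variance explained, f is 0.229 and 0.240.

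The multiplicity result below does not depend on that difference.

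**Number of comparisons.**

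- Constructs (Outcomes): 7, or 8 if suicidal behaviour and ideation are separated.
- Follow-ups (Outcomes, Statistical methods): 2.
- Baseline-adjusted comparisons: 7 × 2 = 14, or 8 × 2 = 16.

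The trend models are left out of the count because they reuse the same data. Extra scores are also left out. Outcome measures lists the BSS, BRFL-A and SBQ-14 for suicidality, and help-seeking intentions plus three yes/no subscales of actual help-seeking. The document does not say which of these carry the primary label. Including any of them would raise the error rate, by an amount not calculated here.

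**Independent tests.** With no true effect on any outcome (the global null) and each test at 0.05, the chance of at least one false positive is 1 − 0.95^k:

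- k = 7: 30.2%
- k = 8: 33.7%
- k = 14: 51.2%
- k = 16: 56.0%

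**Correlated tests.** These outcomes will be correlated, and the document gives no values, so the correlations are assumptions. Test statistics were simulated as normal variables with a common correlation between outcomes. The 18-month statistic was set to r × (12-month statistic) + √(1 − r²) × (an independent set with the same between-outcome correlation). Each was tested two-sided at 0.05, with 400,000 draws per setting.

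| Between outcomes | Between follow-ups (r) | 14 tests | 16 tests |
|---|---|---|---|
| 0.3 | 0.5 | 44.5% | 48.3% |
| 0.3 | 0.7 | 41.4% | 45.1% |
| 0.5 | 0.5 | 38.2% | 41.3% |
| 0.5 | 0.7 | 35.6% | 38.4% |
| 0.7 | 0.5 | 30.3% | 32.3% |
| 0.7 | 0.7 | 28.0% | 29.8% |

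At a single follow-up, with between-outcome correlations of 0.3 to 0.7, the chance is 27.1% down to 17.8% for seven tests and 29.8% down to 19.1% for eight. Naming a time point therefore helps but is not enough.

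**Cost of adjusting.** By normal approximation, the detectable f is (z for the two-sided level + z for 80% power) × √0.95 / √N. With N = 144:

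- level 0.05: (1.960 + 0.842) × 0.975 / 12 = 0.23
- level 0.05/8 = 0.00625: (2.734 + 0.842) × 0.975 / 12 = 0.29
- level 0.05/16 = 0.0031: 0.31

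**The case against.** **The 0.05 is not an analysis rule.** It appears only as an input to the power calculation, and Statistical methods names no level. A reader might infer that the plan commits to 0.05 for every primary test; the document does not say so. This stands, and the percentages above are therefore conditional on that reading. The document offers no other level.

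**Adjustment may be specified elsewhere.** This is a condensed article, and a full protocol or SAP may contain a multiplicity rule. A reader might infer that the trial has no multiplicity control at all; one article cannot show that. What survives is narrower. The article itself makes all the constructs primary at both follow-ups and powers the trial at an undivided 0.05. A later division of that level would not match the detectable effect size it reports.

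**The aim already gives a lead.** It does point to suicidal and self-harming behaviour, and that is the natural source for a fix. It selects no variable or time point, however, and Outcomes overrides it with an unranked list.

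**The outcomes are correlated.** Independence is implausible for depression, hopelessness and self-esteem measured twice in the same people, so 51% to 56% is an upper figure for these counts. The correlated results still lie far above 5%.

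**Does the power calculation imply an endpoint?** A reader might infer that it describes a particular analysis, such as the BSS total at 12 months. It names neither. The BSS is described as measuring ideation and intent, while the aim concerns behaviour, so that choice cannot be read out of the sample size section.

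**Conclusion.** The point holds as a defect in what the article fixes: an unranked set of seven or eight primary outcomes, each compared at two follow-ups, with no lead outcome or time point. At 0.05 per comparison, the chance of at least one false-positive primary result is 51% to 56% if the tests are independent and roughly 28% to 48% over the assumed correlations.

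These figures rest on three assumptions: no effect on any outcome, 0.05 applied to each test, and correlations that the document does not supply. They should be quoted as a range and not as the trial's known error rate. Counting seven constructs or eight does not change the conclusion. Even the most favourable setting in the table, 28%, is more than five times the nominal level.

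**What to change.** Before unblinded analysis, name one primary outcome variable, one time point and one model. The sponsor should choose the variable from the domain that the aim and hypothesis 1 put first, analyse it with the baseline adjustment already given in Statistical methods, and relabel the other outcomes and the other follow-up as secondary. This changes wording only. The price is that separate unadjusted primary claims on each scale are given up.

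If several outcomes must remain primary, apply Holm across them at one named time point and restate the detectable effect size at the adjusted level. For eight tests at 144 analysed, the Bonferroni level, which is Holm's first step, moves the detectable f from about 0.23 to about 0.29. The article already reports the actual sample as 165, so enlarging recruitment cannot be assumed as a way to recover that power.

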### Outcome measures

Basic demographic details, including age, gender, employment or educational status, living circumstances, country of birth, parents' or guardians' employment status, parents' or guardians' country of birth, medical history and details of any treatment being received, are recorded on a specifically designed, standardised questionnaire.

Axis-I diagnoses will be assessed using the Structured Clinical Interview for DSM-IV [19].

Depression will be assessed by the Center for Epidemiologic Studies - Depression scale [20] a 20-item measure of current level of depressive symptomatology. A cut off score of 24 was used in this study in order to detect symptoms more likely to be of clinical significance [21].

The Beck Scale for Suicidal Ideation (BSS) [22] measures suicidal ideation and intent. This is a 19 item self-report scale with items rated on a 3-point scale (0-2). The total score ranges from 0 to 38. Higher scores indicate greater suicidal ideation.

The Brief Reason for Living Inventory - Adolescent Version (BRFL-A) [23] is a self-report instrument that assesses suicide ideation and behaviour. Higher scores, as rated on a 6-point scale (1 = not at all important to 6 = extremely important), indicate greater reasons for living.

The Suicidal Behaviours Questionnaire (SBQ-14) [24] measures five domains: past suicidal ideation, future suicidal ideation, past suicide threats, future suicide attempts, and the likelihood of dying in a future suicide attempt. These domains are rated across a number of time points: (1) the past several days including today, (2) past month, (3) past four months, (4) past year, and (5) lifetime. The SBQ-14 also assesses the number of episodes of DSH and suicide intent during the past year. In the present study, this section of the questionnaire was modified to assess lifetime and past month ratings of self-injurious behaviour and suicide intent in order to provide more specific information about chronicity and current risk of suicidal behaviour.

The Beck Hopelessness Scale [25] measures hopelessness. This is a 20-item true-false scale that measures the extent of negative attitudes about the future. A total score is obtained by summing the ratings with a potential scoring range of 0-20. High scores reflect greater hopelessness.

The Rosenberg Self-Esteem scale [26] is a 10-item measure of global self-worth. Statements are rated on Likert scale ranging from strongly agree (1) to strongly disagree (4), with a total scale range of 10-40. Low versus high self esteem was dichotomized using a cut-off score of 20, with scores of below 20 indicating high self-esteem and scores of 20 or above indicating low self-esteem.

The Multidimensional Scale of Perceived Social Support [27] measures perceived social support. This 12-item instrument includes items rated on a 7-point scale ranging from "very strongly agree" to "very strongly disagree". The total score ranges from 12-84 with a higher score indicating a greater level of perceived social support.

The General and Actual Help Seeking Scales [28] measure help-seeking intentions, appraising both formal and informal sources. Participants rate help-seeking intentions ranging from 1 ("extremely unlikely") to 7 ("extremely likely") for each help source option including "no one". Higher scores indicate higher intentions. The AHSQ measures actual help-seeking behaviour. In this study participants were asked whether help had been sought for "an emotional problem" within the last two weeks. Generally, this measure is reported as three subscales: whether or not informal help has been sought; whether or not formal help has been sought; and whether or not any help has been sought.

### Sample size calculation: effect size and statistical power

Suicide and SA rates from other studies vary between 3.9% and 15.1% for a contact group, and 4.6% and 17.3% for a non-contact group [11,10], with small effect sizes. The design of our study differs from previous studies and it is not possible to make any firm inference for our study, although it is reasonable to expect a similar effect size. The power analysis for this study is based on using the general linear model to compare the intervention and control groups with the baseline values of an outcome measure as the covariate. It is assumed (conservatively) that the covariate would explain 5% of the variance in the dependent variable. Based on previous research at this centre, we expect to recruit 180 subjects who would be equally allocated to the two groups and conservatively estimated a drop-out rate of 20%. A power calculation indicated that we would be able to detect a small effect size of 0.21 with a significance level of 0.05 and power of 0.8. The actual sample size (n = 165) has made only a small change to the power calculation - the detectable effect size has increased from 0.21 to 0.22.

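### The sample-size section treats the effect it expects from the cited attempt rates and the effect it can detect as alike, but on a common scale the cited effects are several times smaller and the trial has about 5–10% power for them

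*Protocol article*

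**What the plan says.** All the figures stand in one paragraph of the protocol article, under *Sample size calculation: effect size and statistical power*.

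- Prior evidence: "Suicide and SA rates from other studies vary between 3.9% and 15.1% for a contact group, and 4.6% and 17.3% for a non-contact group", which the text describes as small effects.
- Expectation for this trial: "it is not possible to make any firm inference for our study, although it is reasonable to expect a similar effect size".
- Planned size: "we expect to recruit 180 subjects who would be equally allocated to the two groups", with 20% drop-out.
- Claim: "we would be able to detect a small effect size of 0.21" "with a significance level of 0.05 and power of 0.8", from a general linear model with the baseline value as covariate. At the actual n = 165, "the detectable effect size has increased from 0.21 to 0.22".

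The section does not name the metric of the 0.21 or convert the cited rates to it. Under *Aims and hypotheses* the purpose is to "determine if suicidal and self harming behaviour can be reduced", and *Outcomes* lists suicidal behaviour first among the primary outcomes.

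**The concern.** The same adjective, small, is used for the cited effects and for the detectable effect, and the sentence between them says that a similar effect is reasonable to expect. The natural conclusion is that the trial can detect about what it expects. The first figure is a difference between two event proportions. The second is a standardised difference on a score in a linear model. Whether they are alike can be judged only on a common scale.

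The interpretation of a null result is at stake. Reducing suicidal behaviour is the stated aim, and the only prior evidence of effect in the section concerns suicide and attempts. If the trial has almost no power for differences of that size, a non-significant result on attempts says very little, yet a reader relying on the stated 80% could take it as evidence that postcards do not work in young people.

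**Working it through.** **Inputs.** From the sample-size section: α = 0.05, power 0.80, N = 180 (90 per arm) and 165, drop-out 20% (180 × 0.8 = 144, or 72 per arm; 165 × 0.8 = 132, or 66 per arm), covariate explaining 5% of variance, and the four rates. Two assumptions: the test is two-sided (not stated), and the rates pair by study. The pairing is the only one that fits effects described as small: 17.3% v 3.9% would give h = 0.46, and 4.6% v 15.1% would reverse the direction.

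**1. Reproduce 0.21 and 0.22.** Solve the noncentral F power equation (1 and N − 3 df, noncentrality f²N) for 80% power.
- N = 180: f = 0.210. N = 165: f = 0.219.
- Both stated figures are recovered as Cohen's f, with drop-out and covariate left out. For two equal groups d = 2f, so d = 0.42 and 0.44.
- Read as d, 0.21 does not fit: power at 72 per arm is about 25%.

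**2. Put the cited rates on the same scale.** h = 2·asin√p₁ − 2·asin√p₂. The linear version is d = (p₁ − p₂)/√[p̄(1 − p̄)], with f = d/2.

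| Pair | h | d (linear) | f |
|---|---|---|---|
| 17.3% v 15.1% | 0.0597 | 0.022/√(0.162 × 0.838) = 0.0597 | 0.030 |
| 4.6% v 3.9% | 0.0347 | 0.007/√(0.0425 × 0.9575) = 0.0347 | 0.017 |

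Ratios to the stated figures: 0.21/0.02985 = 7.0 and 0.22/0.02985 = 7.4; 0.21/0.01735 = 12.1 and 0.22/0.01735 = 12.7.

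**3. Check with a logit conversion.** d = |ln OR| × √3/π. The odds ratios are 0.850 and 0.842, so d = 0.089 and 0.095. Against d = 0.42–0.44 the gap is 4.4 to 4.9 times. It reaches 5.5 times if the detectable effect is recomputed after drop-out (0.49/0.0895).

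**4. Power for the cited differences.** With SE₀ = √[2p̄(1 − p̄)/n] and SE₁ = √{[p₁(1 − p₁) + p₂(1 − p₂)]/n}, two-sided power is Φ[(Δ − 1.96·SE₀)/SE₁] + Φ[(−Δ − 1.96·SE₀)/SE₁].

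For 17.3% v 15.1% at n = 72: SE₀ = 0.0614, SE₁ = 0.0614, giving Φ(−1.60) + Φ(−2.32) = 0.0545 + 0.0102 = 0.065.

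| Per arm | 17.3% v 15.1% | 4.6% v 3.9% |
|---|---|---|
| 66 | 6.4% | 5.5% |
| 72 | 6.5% | 5.5% |
| 90 (no drop-out) | 6.9% | 5.6% |

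Using the logit-scale d in the linear model with the 5% covariate, power is 8.2% to 10.0% over the same range. If the test were one-sided at 0.05, the same formula with 1.645 and the upper tail only gives 7.4–10.7%. Φ[d√(n/2)/√0.95 − 1.645] with the logit-scale d gives 13–16%.

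**5. Scale of the shortfall.** For 80% power, n per arm = {1.96√[2p̄(1 − p̄)] + 0.8416√[p₁(1 − p₁) + p₂(1 − p₂)]}²/Δ², which is about 4,402 and 13,036 before drop-out. At 66–72 per arm, a control rate of 17.3% would have to fall to about 2.8–3.2% for 80% power. From 4.6%, even eliminating all events gives only 42–45%. The 95% CI half-width for a risk difference near 16% is 1.96√(2 × 0.16 × 0.84/66) = 12.5 points (12.0 at 72 per arm), against a cited difference of 2.2 points.

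**The case against.** The strongest reply is that the section never claims 80% power for event proportions. It takes the sample size from feasibility, specifies a general linear model with a baseline covariate, and reports the detectable effect. It also hedges, since the prior studies differ in design and no firm inference is possible. That stands. A reader might infer that the protocol promises 80% power on suicide attempts and delivers about 6%; the text does not support that.

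The endpoint is a further difficulty. *Outcome measures* assesses suicidal behaviour with the SBQ-14, which has rated domains and episode counts, and *Statistical methods* applies the linear model to each outcome. No proportion-with-an-attempt endpoint or two-proportion test is named. The power figures above therefore describe what the trial could learn about differences like those cited, not a planned test. The cited rates cover suicide and attempts only, so it is also tempting, but unsupported, to apply the numbers to deliberate self-harm.

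The size of the gap depends on the scale. The metric of the 0.21 is unnamed, the pairing is assumed, and the logit conversion shrinks the ratio. Read as d, the ratio to the cited effects would be 3.5 to 6.3, although the stated 80% then fails. A single multiplier would claim too much.

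None of this rescues the sentence. A similar effect is the only expectation the section offers, it rests only on event rates, and no conversion brings those rates near the detectable effect.

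**Conclusion.** The point holds as a mismatch between rationale and detectable effect; the stated 0.21 and 0.22 themselves reproduce. The cited differences are roughly 7 to 13 times smaller than the detectable effect on the f scale, and about 4 to 5.5 times smaller on a logit conversion. Two-sided power for a difference of that size in the proportion with an attempt is about 5–7%, and no more than about 10% on the logit conversion.

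This rests on pairing the rates by study, on reading 0.21 as Cohen's f (the power figures for the two proportions do not need this), and on a two-sided test. A one-sided test would raise power to at most about 16%, which leaves the conclusion unchanged. No numerical conclusion is drawn for deliberate self-harm.

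**What to change.** In the sample-size section:

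1. Replace the sentence on a similar effect size with a statement that the cited event-rate differences (h about 0.06 and 0.035 if paired by study) lie far below the detectable effect, and that the trial has only about 5–10% power for them (two-sided).
2. Name the metric of the 0.21 and 0.22, and limit the 80% claim to outcomes analysed as continuous scores.
3. State that suicide attempts will be reported as an estimate with a 95% CI, and that a non-significant result on them is not evidence of no effect.

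The change is wording only. It needs no additional participants and no change of design, so it can still be made with recruitment at 165. The price is a less favourable stated expectation for suicidal behaviour.

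### On a two-sided test, the detectable effects of 0.21 and 0.22 match the full enrolled numbers and do not follow from the stated 20% drop-out; as Cohen's f they are not small

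*Protocol article*

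**What the plan says.** The protocol article, under Sample size calculation, bases power on "using the general linear model to compare the intervention and control groups with the baseline values of an outcome measure as the covariate". Its inputs are:

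- Recruitment: "we expect to recruit 180 subjects who would be equally allocated to the two groups".
- Drop-out: the authors "conservatively estimated a drop-out rate of 20" per cent.
- Covariate: it is assumed that "the covariate would explain 5% of the variance in the dependent variable".

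The result is that "we would be able to detect a small effect size of 0.21 with a significance level of 0.05 and power of 0.8". For the 165 participants actually recruited, "the detectable effect size has increased from 0.21 to 0.22".

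The paragraph names neither the effect-size metric nor the sidedness of the test. Two other sections bear on sidedness. Under Statistical methods, "the general linear model will be used to test for the treatment factor" at each follow-up. Under Aims and hypotheses, the hypotheses are worded by direction, for example "1. Decreased suicidal behaviour and ideation 2. A reduction in depression and hopelessness". The sample-size paragraph also describes the effects in the earlier contact studies as small and expects something similar here.

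**The concern.** The paragraph prints its inputs and its result, so the result can be checked, and the two do not appear to agree. If 20% of participants are lost, the detectable effect should be the one for 144 analysed (or 132 from 165), yet the printed values look like those for everyone enrolled.

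The label is a second problem. An effect of 0.21 called small, with no metric, invites reading as a standardised mean difference of 0.21. The paragraph uses the same word for the earlier effects that it hopes to match, so it suggests that the trial is powered for an effect of that size. If it is not, a null result says little about effects of the expected size, and the power statement should not suggest otherwise.

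**Working it through.** **Inputs.** All come from the sample-size section: 180 planned and 165 actual, equal allocation, 20% drop-out, R² = 0.05 for the covariate, level 0.05, power 0.80. Sidedness is not stated, so both are tried.

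**Analysed numbers.** 180 × 0.80 = 144; 165 × 0.80 = 132.

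**Method.** F test of a two-level factor with one covariate: 1 and N − 3 degrees of freedom, noncentrality λ = N f² / (1 − R²), solved for the f that gives power 0.80. With two equal groups, d = 2f. The one-sided version uses the noncentral t with the same noncentrality, √λ. Setting R² = 0 stands for no covariate gain; it also covers the case where f is expressed on the residual standard deviation.

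**Step 1: reproduce the printed figures, and compare with the stated inputs.**

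| Analysed N | Two-sided, R² = 0 | Two-sided, R² = 0.05 | One-sided, R² = 0 | One-sided, R² = 0.05 |
|---|---|---|---|---|
| 180 (no drop-out) | **0.2100** | 0.2046 | 0.1860 | 0.1813 |
| 165 (no drop-out) | **0.2194** | 0.2139 | 0.1944 | 0.1895 |
| 144 (180 less 20%) | 0.2351 | 0.2291 | **0.2082** | 0.2029 |
| 132 (165 less 20%) | 0.2457 | 0.2395 | **0.2176** | 0.2120 |

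Bold pairs round to the printed 0.21 and 0.22. For the two-sided pair, the smallest N with 80% power is exactly 180 at f = 0.21 and exactly 165 at f = 0.22. With both stated inputs applied (lower two rows, R² = 0.05), the result is 0.23 and 0.24 two-sided, or 0.20 and 0.21 one-sided. Neither is the printed pair.

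**Step 2: hand check by normal approximation, R² = 0.** f ≈ (1.960 + 0.842) / √N.

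- N = 180: 2.802 / 13.416 = 0.209
- N = 165: 2.802 / 12.845 = 0.218
- N = 144: 2.802 / 12 = 0.233
- N = 132: 2.802 / 11.489 = 0.244

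Multiplying the last two by √0.95 = 0.975 for the covariate gives 0.228 and 0.238. These agree with the exact values to within 0.002.

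**Step 3: power at the printed effects after drop-out, two-sided.**

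- N = 144, f = 0.21: 70.6% (R² = 0), 72.8% (R² = 0.05)
- N = 132, f = 0.22: 70.8% (R² = 0), 73.0% (R² = 0.05)

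To keep 80% power at f = 0.21 with 20% drop-out would take 172 / 0.80 = 215 recruits (R² = 0.05) or 180 / 0.80 = 225 (R² = 0).

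**Step 4: which metric is 0.21?** Read as d = 0.21, a two-sided test needs 678 (R² = 0.05) to 712 (R² = 0) analysed participants, far more than this trial has. Read as f, the figure is of the right order. So 0.21 is Cohen's f, and d = 2 × 0.21 = 0.42 (0.22 gives d = 0.44). The usual benchmarks are 0.10 small and 0.25 medium for f, and 0.5 medium for d.

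**Step 5: compare with the earlier effects.** The paragraph quotes event rates of 3.9% to 15.1% with contact and 4.6% to 17.3% without. It does not say how they pair. Assuming low with low and high with high, Cohen's h = 2 arcsin √p₂ − 2 arcsin √p₁ is 0.035 (3.9% against 4.6%) and 0.060 (15.1% against 17.3%). These are for a binary outcome and so are only roughly comparable with d, but a detectable d of 0.42 is 7 to 12 times as large (0.42 / 0.060 = 7; 0.42 / 0.035 = 12).

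**The case against.** The strongest defence is a one-sided test. The article states no sidedness and its hypotheses are directional. A one-sided 0.05 test on 144 and 132 analysed, without covariate gain, gives 0.208 and 0.218, which round to the printed values, with power of 80.6% and 80.8% at 0.21 and 0.22. This stands as far as it goes. A reader might infer that the figures can arise only if nobody drops out, or that the authors demonstrably left drop-out out of the calculation. The document does not support either: the first is false if the test was one-sided, and the second is an inference from matching numbers.

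The defence has limits. No one-sided test is declared, directional hypotheses do not declare one, and testing a treatment factor in a general linear model is ordinarily two-sided. It also needs the 5% covariate to bring no gain, or f to be on the residual standard deviation. The two-sided, no-drop-out match needs the same condition, so that condition does not separate the two readings.

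A second defence is that 5% is described as conservative. Two-sided, after drop-out, a covariate explaining about 20% of variance would restore f = 0.21 and 0.22. That may hold for some outcomes, but it is not the stated assumption.

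Third, the discrepancy is modest and the numbers were set by expected recruitment, not solved from an effect. This is right, and it limits the weight of the point.

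Lastly, a reader might conclude that the trial has only about 25% power. That follows only if 0.21 is taken as d with 144 analysed, a reading that the trial's own numbers rule out. It is not a property of this calculation.

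**Conclusion.** The point holds on the conventional two-sided reading. The printed 0.21 and 0.22 then correspond to 180 and 165 analysed with no covariate gain, and they contradict the paragraph's own 20% drop-out. With that drop-out, the detectable f is 0.229 to 0.235 for 180 recruited (d = 0.46 to 0.47) and 0.240 to 0.246 for 165 (d = 0.48 to 0.49). Two-sidedness is an assumption, supported by the planned analysis but not stated.

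Independently of sidedness, two things stand. The stated drop-out and covariate together, with the covariate credited on the raw standard deviation, do not yield the printed pair. And the word small is misleading, because f = 0.21 is d = 0.42, nearer medium than small. The label is the more consequential of the two, since it blurs the gap between the effect the trial can detect and the effect it says it expects. Neither changes the design or the planned analysis.

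**What to change.** Restate the result along these lines: *With 165 randomised, 20% drop-out (132 analysed) and a baseline covariate explaining 5% of variance, a two-sided test at 0.05 has 80% power for Cohen's f = 0.24 (d = 0.48). The planned 180 (144 analysed) would have given f = 0.23 (d = 0.46).* Name the metric and delete the word small.

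If a one-sided test was intended, declare it in the sample-size and statistical methods sections and restate accordingly. With both stated inputs, the figures would then be f = 0.21 (d = 0.42) for 165 and f = 0.20 (d = 0.41) for 180.

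The cost is wording only. No further participants are needed and the analysis does not change; on the two-sided reading the stated figure becomes slightly less favourable.
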